### Participant timeline {13}

Time schedule of enrollment, interventions, and assessments is illustrated in Table 2.

**Table 2 Tab2:**
[figure not shown]
Time schedule of enrolment, interventions, and assessments

*CT* computed tomography, *ECG *electrocardiogram, *GO-QoL* Graves' ophthalmopathy quality of life questionnaire, *HCQ* hydroxychloroquine.
* *ECG* was performed in treatment group to rule out *HCQ*-related *QT* prolongation

### Sample size {14}

The sample size was estimated using Stata software. Due to the lack of literature on the effects of HCQ for mild GO, we referred to the clinical trial published by the NEJM in 2011, which investigated the efficacy of selenium in patients with mild GO [4]. Approximately 12% of GO patients showed spontaneous improvement, and the use of selenium significantly increased this improvement rate to 37% (absolute difference of 25%). We hypothesized that HCQ improves the prognosis of mild GO patients by at least the same proportion as selenium, i.e., 25% of improvement rate [3]. As selenium is now considered a recommended treatment option for mild GO in clinical guidelines, we reasoned that hydroxychloroquine should demonstrate at least comparable efficacy to warrant further investigation. Based on a 2:1 random allocation ratio, a two-sided *α* of 0.05, and 80% power, the estimated sample size was 72 participants in the HCQ group and 36 in the control group.

### Recruitment {15}

We will collaborate with endocrinologists and ophthalmologists at the Taipei, Bei-Hu, Cancer Center, and Hsin-Chu branches of National Taiwan University Hospital to screen potential candidates eligible for the study.

### Assignment of interventions: allocation {16a, 16b, 16c}

A total of 108 participants will be randomly assigned into experimental group and control group with a 2:1 allocation. The randomization process will be independently constructed by the National Taiwan University Hospital Statistical Consulting Unit (NTUH-SCU). Randomization sequence will be created using SAS 9.4 (SAS Institute Inc, Cary, NC). The result of randomization will be delivered to principal investigators via Research Electronic Data Capture (REDCap) system, version 14.3.3, a secure web-based application by Vanderbilt University.

### Assignment of interventions: blinding {17a, 17b}

This study is an open-label study, so all participants and treating physicians will be unblinded. To minimize detection bias, ophthalmologists performing outcome assessments will be blinded to group allocation. They have no role in randomization or participant assignment and will perform standardized evaluations without access to treatment status.

### Data collection and management {18a, 19}

Study nurses will make appointments with patients to ensure essential data are collected completely, including baseline information, lab data, GO-QoL, orbital CT, and ophthalmic examinations according to study schedule (Table 2). All clinical data will be recorded in standardized case report forms (CRFs) by trained study nurses at each study site. After data collection, information will be stored electronically in either the electronic medical record system or the REDCap platform, a centralized, password-protected database accessible only through the internal hospital network to ensure privacy and confidentiality. All data entries will be validated through regular data audits, range checks, and periodic double-entry verification for critical variables. Access to the database will be restricted to authorized personnel only. Data will be anonymized using participant identification codes. The database is hosted on a secure institutional server with regular backups and encryption protocols to ensure data integrity and confidentiality. Detailed data collection in this study is shown as below:
Basic information: At the time of enrollment, we will collect participants’ age, gender, nationality, smoking status or exposure to secondhand smoke, types of thyroid disease, treatments received for thyroid disease in the past, current medications, duration of eye symptoms, and autoimmune diseases. Additionally, it is necessary to inquire if the patient is pregnant or planning to become pregnant, and a urine pregnancy test may be conducted if needed to rule out the possibility of pregnancy.GO-QoL will be obtained at enrollment and at the 12th, 24th, and 48th weeks. This internationally recognized questionnaire, validated for both quantification and validity, will be administered by study nurses [13]. It is designed to assess the quality of life in patients with GO, focusing on two main aspects: visual functioning and appearance subscales. Scores for each aspect are calculated separately, with a maximum score of 100 points each; lower scores indicate a greater impact on quality of life. This questionnaire has been translated into traditional Chinese and used in prior research and published internationally [17].Ophthalmological examinations will be conducted by the same ophthalmologist in each hospital. Three main metrics will be measured: eyelid aperture, soft tissue involvement, and exophthalmos using a Hertel exophthalmometer. These metrics are the primary outcomes of the study. Other assessments, including diplopia evaluated using the Gorman score [15], clinical activity score, and visual acuity, will also be recorded in detail. Given the potential side effect of hydroxychloroquine causing retinopathy [18], ophthalmologists will perform baseline and follow-up retinal toxicity assessments, including optical coherence tomography (OCT) and automated visual field testing when indicated.Orbital non-contrast CT will be conducted to evaluate changes in CT measurement values before enrollment, after medication, and after discontinuation of medication. Measurements for orbital volumetry will be based on a unified method adopted in numerous studies [14]. Parameters will include muscle volume (MV), fat volume (FV), orbital volume (OV), MV/OV ratio, FV/OV ratio, exophthalmos length (distance from interzygomatic line to the apex of the cornea), mean density of muscle, and mean density of fat.

### Collection, laboratory evaluation, and storage of biological specimens {33}

Blood specimens will be collected via venipuncture, then centrifuged and aliquoted into Eppendorf tubes, and stored at − 80 °C. Laboratory evaluations will include thyroid function tests (free thyroxine [free T4], thyroid-stimulating hormone [TSH]), thyroid autoantibodies (TBII, anti-thyroid peroxidase [anti-TPO], and anti-thyroglobulin antibody [ATA]), complete blood count with differential, liver function tests (AST, ALT), inflammatory markers (interleukin-6 [IL-6], interleukin-1β [IL-1β], tumor necrosis factor-α [TNF-α], and interferon-γ [IFN-γ]), fibrosis marker (transforming growth factor-β [TGF-β]), and serum hyaluronic acid levels. Additional serum and plasma samples will be stored at − 80 °C for up to 20 years for future research related to autoimmune or thyroid-related diseases, in accordance with participants’ informed consent and institutional ethics approval. All remaining biospecimens will be destroyed at the end of the storage period in compliance with institutional biosafety protocols.

### Statistical methods {20a, 20b, 20c}

Basic characteristics will be presented using descriptive statistics, including mean (standard deviation) and number of occurrences (percentage). For non-normally distributed data, the median (interquartile range, IQR) will be used. To compare between the treatment group and the observation group, depending on the nature of the data, Student’s *t*-tests will be used for continuous variables, and chi-square tests or Fisher’s exact tests will be used for categorical variables, to examine the differences between the two groups.

To compare the scores of the GO-QoL and the CAS before and after treatment, two-sided *t*-tests and Mann–Whitney tests will be used. Pearson’s correlation analysis will be utilized to test the association and determine the correlation coefficient (*r*) among variables of interest. The severity of thyroid eye disease before and after treatment in both groups will be compared in terms of the proportion of patients who show improvement, stability, or deterioration. One-way repeated measures analysis of variance (ANOVA) will be used to analyze the change of variables before and after treatment. In addition to ANOVA, ANCOVA and regression models will be used to adjust for baseline differences and estimate effect sizes with confidence intervals.

Exploratory subgroup analyses will be performed to assess whether treatment effects differ by age, gender, baseline TBII levels, duration of GO, and smoking status. These analyses are intended to explore potential effect modifiers and will be interpreted cautiously given the limited sample size. A two-tailed *P* value < 0.05 will be considered statistically significant. Statistical analysis will be performed using Stata/SE 14.0 for Windows (StataCorp, College Station, TX, USA).

All randomized participants, including those who discontinue the intervention prematurely, will be included in the primary analysis based on the intention-to-treat (ITT) principle. Sensitivity analyses will be conducted if necessary to evaluate the robustness of results in the presence of missing data. Missing data will be handled using multiple imputation under the assumption of missing at random (MAR).

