### Trial design {8}

This is a multi-center open-label interventional randomized controlled trial (RCT) comparing the effects of HCQ versus observation in patients with mild GO in Taiwan. The allocation ratio of randomization will be 2:1 in HCQ and control group, respectively. This trial adopts a superiority framework, hypothesizing that the addition of hydroxychloroquine to standard of care will result in superior ophthalmic outcomes compared to standard of care alone in patients with mild GO.

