### Outcomes {12}

Primary endpoint of this study is the composite ophthalmic outcome of ophthalmic examinations including eyelid aperture, soft tissue involvement, and exophthalmos at the 24th week and 48th week of study, with definitions in line with the previous literature for comparison [4]. 

The primary endpoint is a composite ophthalmic outcome assessed at weeks 24 and 48. Based on predefined criteria (as shown in Table 1), participants will be classified as follows:Improvement: achievement of at least one improvement criterion in any domain, without meeting any deterioration criteria in the othersDeterioration: meeting any deterioration criterion in one or more domainsStable: neither improved nor deteriorated in any domain

**Table 1 Tab1:** Definition of the composite ophthalmic outcome (primary endpoint)

Ophthalmic domain	Measure	Result classifications		
		Improvement	Stable	Deterioration
Eyelid aperture	Slit lamp	Decrease by ≥ 2 mm	Neither improved nor deteriorated	–
Soft tissue involvement	NOSPECS class 2 signs	Reduction of ≥ 1 grade in NOSPECS class 2 signs		1. Increase ≥ 1 NOSPECS class 2. New NOSPECS class
Exophthalmos	Hertel exophthalmometer	Decrease by ≥ 2 mm		–
Other ophthalmic signs				Vision acuity deterioration or other evidence of optic nerve compression

NOSPECS is a clinical classification system for assessing the severity of Graves’'orbitopathy [7], consisting of the following seven classes (class 0–6):

Class 0: No signs or symptoms; Class 1: Only signs, no symptoms (e.g., lid retraction); Class 2: Soft tissue involvement (e.g., periorbital edema, conjunctival injection, chemosis); Class 3: Proptosis; Class 4: Extraocular muscle involvement; Class 5: Corneal involvement; Class 6: Sight loss due to optic nerve compression

In this study, improvement or deterioration in soft tissue involvement is assessed based on changes in class 2 severity. Deterioration is defined as a worsening of at least one grade in any NOSPECS class, or the appearance of a new class not previously present Improvement: achievement of at least one improvement criterion in any domain, without meeting any deterioration criteria in the others Deterioration: meeting any deterioration criterion in one or more domains Stable: neither improved nor deteriorated in any domain

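### With 2:1 allocation, Student's t-test and ordinary ANCOVA/regression standard errors depend on equal variances for the continuous secondary outcomes; Welch's test and robust standard errors remove that dependence cheaply

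*Protocol article*

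**What the plan says.** In the Protocol article, Statistical methods {20a, 20b, 20c}, the comparison of the two groups depends on the type of variable: "Student’s *t*-tests will be used for continuous variables", while "chi-square tests or Fisher’s exact tests will be used for categorical variables". The same section adds t-tests and Mann–Whitney tests for GO-QoL and CAS. It assigns baseline adjustment, effect sizes and confidence intervals to ANCOVA and regression models. It states no variance assumption, no SD and no unequal-variance option.

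Trial design {8} fixes the split: "The allocation ratio of randomization will be 2:1 in HCQ and control group, respectively". Sample size {14} gives the arm sizes: "the estimated sample size was 72 participants in the HCQ group and 36 in the control group".

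Outcomes {12} defines the primary endpoint: "The primary endpoint is a composite ophthalmic outcome assessed at weeks 24 and 48". It is classified as improvement, stable or deterioration, so it is categorical.

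**The concern.** Student's two-sample test, as the name is normally used, estimates one common variance from both arms. With equal arms this does little harm when the SDs differ. With a 2:1 split the larger arm dominates the pooled estimate, although the smaller arm contributes most of the uncertainty in the difference.

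- If HCQ (the larger arm) is the more variable, the standard error is too large, the test is conservative and power is lost.
- If control (the smaller arm) is the more variable, the standard error is too small and type I error rises.

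ANCOVA and linear regression with ordinary standard errors share the assumption, so the planned confidence intervals inherit the problem. At stake are the P values and intervals for CT volumes and densities, antibodies, serum markers and, in part, GO-QoL and CAS. Either direction is conceivable. A response in only some participants would widen the HCQ arm. For a marker whose spread rises with its level, a drug that lowers the level would leave the control arm wider.

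**Working it through.** **1. The plan's own figure.** Sample size {14} starts from "Approximately 12% of GO patients showed spontaneous improvement", against 37% with treatment, with "a two-sided *α* of 0.05, and 80% power" and 2:1 allocation. Using the pooled-variance formula for two proportions without continuity correction:

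- Mean proportion = (0.12 + 2 × 0.37)/3 = 0.2867, and 0.2867 × 0.7133 = 0.2045.
- Null term: 1.960 × √(0.2045 × 1.5) = 1.0855.
- Alternative term: 0.8416 × √(0.12 × 0.88 + 0.37 × 0.63/2) = 0.8416 × √0.2222 = 0.3967.
- Control n = (1.0855 + 0.3967)²/0.25² = 35.1, rounded up to 36. HCQ n = 72, total 108.

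The stated 72 + 36 is reproduced. It rests on a binary rate, so no t-test enters it.

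**2. How far pooling misstates the standard error.** Let s be the HCQ/control SD ratio, with the control SD set to 1.

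- Expected pooled variance of the difference: [(72s² + 36)/108] × (1/72 + 1/36) = (2s² + 1)/72.
- True variance of the difference: s²/72 + 1/36 = (s² + 2)/72.
- Ratio of pooled to true standard error: √[(2s² + 1)/(s² + 2)].

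At s = 1.5 this is √(5.5/4.25) = 1.138. At s = 2/3 it is √(1.889/2.444) = 0.879. At s = 1 it is exactly 1.

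**3. Effect on error rate and power.** Normal data were simulated with 72 v 36 participants and 500,000 replicates per setting, at two-sided 0.05. For power, the true difference was set at 2.84 true standard errors, which gives about 80%. The SD ratios are assumptions, because the document gives none.

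| HCQ/control SD | SE ratio | Student type I | Welch type I | Student power | Welch power |
|---|---|---|---|---|---|
| 0.667 | 0.879 | 8.5% | 5.0% | 86.3% | 79.5% |
| 0.8 | 0.929 | 6.8% | 5.0% | 84.1% | 79.8% |
| 1.0 | 1.000 | 4.9% | 5.0% | 80.4% | 79.9% |
| 1.25 | 1.076 | 3.5% | 5.0% | 75.8% | 80.1% |
| 1.5 | 1.138 | 2.6% | 5.0% | 71.9% | 80.3% |

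Student's higher power in the first two rows comes from its inflated error rate and is not a gain. Coverage of a nominal 95% interval is 100% minus the type I error, so it runs from 91.5% to 97.4% over this range.

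**4. The models that supply the intervals.** A simulation of ANCOVA at 72/36 showed the same pattern with ordinary standard errors. With HC3 standard errors the type I error stayed at about 5%. With equal SDs, HC3 cost about 1 point of power.

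**5. Which ratios are plausible.** As an illustration, suppose that 12% of controls and 37% of HCQ participants improve and that improvers shift by d within-group SDs. Each arm's variance is then 1 + p(1 − p)d², where p(1 − p) = 0.106 for control and 0.233 for HCQ. For d = 1, 2 and 3 (assumed), the SD ratio is 1.06, 1.17 and 1.26. A moderate excess in the HCQ arm is therefore compatible with the plan's own improvement rates. Larger ratios would need another mechanism.

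**The case against.** Several counter-arguments are sound and limit the point.

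- **No evidence of unequal variances.** The document gives no SDs, and with equal SDs Student's test is correct. If HCQ has no effect at all on an outcome's distribution, randomisation makes the variances equal and Student's test holds its level. The inflated error rates require equal means with a smaller spread on HCQ. This stands, so the harm is conditional.
- **The intervals come from elsewhere.** A reader might infer that the t-test produces the trial's confidence intervals. The text assigns them to ANCOVA and regression, so changing the t-test alone would leave them untouched. This also stands, and the remedy must cover those models.
- **Not every continuous endpoint rests on this test.** GO-QoL and CAS also have Mann–Whitney tests, GO-QoL change is also classified by a 6-point threshold, and the Student sentence directly follows the description of baseline characteristics. This stands as to reach. Mann–Whitney is not a general remedy for unequal spread, however.
- **The variance option may be in an analysis plan that is not shown.** It may, and the article never uses the word pooled. But it does name a specific test, and the ordinary reading of that name is the equal-variance version. The point concerns what is named, not what is left out.
- **The simulation uses normal data**, while the plan expects some skewed variables. True. The standard-error ratio in step 2 of the working needs only the variances, but the exact error rates depend on normality.

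**Conclusion.** The point holds as a minor improvement to the analysis of continuous secondary and laboratory outcomes. Under 2:1 allocation the named test, and the adjusted models with ordinary standard errors, are valid only if the arms have similar variances. Over assumed SD ratios of 0.67 to 1.5, Student's type I error runs from about 8.5% to 2.6%. Power falls to about 76% and 72% at ratios of 1.25 and 1.5, against 80% for Welch. At ratios near 1 the effect is negligible.

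Three stronger readings are tempting but unsupported. The primary analysis is not compromised: the endpoint is categorical, falls under chi-square or Fisher's exact tests, and its sample size of 108 is reproduced. Power is not lost in both directions: that happens only when the HCQ arm is the more variable, and in the opposite case the fault is false positives. Nor do the documents show that the variances will differ. The case is for protection against an unknown at small cost, not for a demonstrated error.

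**What to change.** In Statistical methods {20a, 20b, 20c}:

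1. Replace Student's t-test with Welch's unequal-variance t-test for between-arm comparisons of continuous variables.
2. State that the ANCOVA and linear regression models supplying effect sizes and intervals will use heteroscedasticity-robust standard errors, for example HC3.

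The cost is a change of wording, with no effect on sample size, data collection or conduct. If the variances turn out equal, about 0.5 point of power is lost with Welch (79.9% v 80.4%) and about 1 point with HC3. The change is best made before outcome data are analysed, so that the choice cannot appear driven by results.

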Secondary endpoints:Changes in GO-Quality of Life Questionnaire (GO-QoL) scores (visual functioning and appearance subscales) at the 24th week and 48th week: A change of 6 points is considered a minimal clinically important difference (MCID). An increase of 6 points in any category is considered improvement, a decrease of 6 points is considered deterioration, and anything in between is classified as stable [13].Changes in non-contrast orbital CT at the 24th week and 48th week, including the ratio and density differences of muscle volume, fat volume, and orbital volume [14].Diplopia will be assessed at the 24th and 48th weeks using the Gorman score, a validated grading system endorsed by the EUGOGO [15]. This scale classifies diplopia into four categories:0—no diplopia1—intermittent diplopia2—inconstant diplopia3—constant diplopia in the primary position or on readingCAS, measured by the 7-point CAS [16], at the 24th week and 48th week.Visual acuity, assessed using best-corrected visual acuity (BCVA, Snellen chart), at the 24th week and 48th week.Changes in serum inflammatory and fibrosis markers at the 24th week and 48th week.Changes in thyroid antibodies at the 24th week and 48th week.

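### The between-arm rules have no method for ordered outcomes, so the 0–3 Gorman diplopia score falls by default to chi-square or Fisher, which ignore the order of its grades

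*Protocol article*

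**What the plan says.** Outcomes {12} lists diplopia among seven secondary endpoints: "Diplopia will be assessed at the 24th and 48th weeks using the Gorman score, a validated grading system endorsed by the EUGOGO". It adds that "This scale classifies diplopia into four categories", numbered from 0 (none) to 3 (constant).

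Statistical methods {20a, 20b, 20c} lets the type of variable decide the between-group test. Continuous variables get Student's t-test. For the rest, "chi-square tests or Fisher’s exact tests will be used for categorical variables". A rank test appears once, for two other outcomes: "To compare the scores of the GO-QoL and the CAS before and after treatment, two-sided *t*-tests and Mann–Whitney tests will be used". Later in the section, "ANCOVA and regression models will be used to adjust for baseline differences and estimate effect sizes with confidence intervals", without naming an outcome or an ordinal model. Diplopia is not mentioned in the section.

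Sample size {14} gives the arm sizes used below: "the estimated sample size was 72 participants in the HCQ group and 36 in the control group".

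**The concern.** The Gorman score is a severity scale, and a useful treatment effect on it is a move towards lower grades. Pearson's chi-square is unchanged if the four grade columns are put in any other order, and the usual extension of Fisher's test to more than two columns shares this property. Such a test spreads its power over three degrees of freedom (four grades minus one), most of them patterns of no clinical interest. A rank test or a proportional-odds treatment effect concentrates on the one direction that matters.

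Two things are at stake. One is power for diplopia with 36 controls. The other is interpretation: an order-blind test can be significant when the arms differ in the spread of grades with almost no net shift. The section is also uneven, since it offers a rank test for CAS, an ordered score, and none for the Gorman score.

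**Working it through.** **The plan's own figure.** Sample size {14} uses 12% vs 37%, 2:1 allocation, "a two-sided *α* of 0.05, and 80% power". The pooled proportion is (0.12 + 2 × 0.37)/3 = 0.2867. With pooled variance and no continuity correction,

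n(control) = [1.960 × √(1.5 × 0.2867 × 0.7133) + 0.842 × √(0.12 × 0.88 + 0.37 × 0.63/2)]² / 0.25² = 35.1, rounded up to 36.

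This gives 36 + 72 = 108, which matches the article. The calculation concerns the primary composite. The article gives no power figure for diplopia.

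**Inputs for diplopia.** The arm sizes (72 and 36) and two-sided 0.05 come from the article. The control grade distributions and odds ratios are assumptions.

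**Effect model.** Under proportional odds, odds(grade ≤ j | HCQ) = OR × odds(grade ≤ j | control) for j = 0, 1, 2. Example: controls 60/25/10/5% have cumulative odds 1.5, 5.67 and 19. At OR 3 these become 4.5, 17 and 57, so the HCQ arm is 81.8/12.6/3.8/1.7%.

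**Chi-square vs rank test.** Power (%) of Pearson chi-square vs tie-corrected Wilcoxon on the follow-up grade, 40,000 simulated trials per cell. The loss in points, taken before rounding, is in brackets.

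| Controls, grades 0/1/2/3 (%) | OR 2 | OR 3 | OR 4 |
|---|---|---|---|
| 85/10/4/1 | 16.2 vs 20.7 (4.6) | 29.7 vs 37.3 (7.6) | 39.7 vs 48.8 (9.1) |
| 70/20/8/2 | 24.0 vs 31.9 (7.9) | 48.5 vs 60.5 (12.0) | 65.1 vs 75.8 (10.7) |
| 60/25/10/5 | 27.9 vs 37.7 (9.8) | 56.5 vs 69.5 (13.0) | 74.4 vs 84.7 (10.3) |
| 40/30/20/10 | 32.6 vs 44.8 (12.2) | 66.8 vs 79.9 (13.1) | 85.5 vs 93.1 (7.6) |

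For controls 40/35/15/10% at OR 2.5, power is 51 vs 66, a loss of about 15 points. With OR = 1, rejection was 3.9–4.8% for chi-square and 5.0–5.1% for the rank test over controls from 70/22/6/2% to 40/35/15/10%. The rank test's gain is therefore not bought with an inflated type I error.

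**Fisher vs rank test** (3,000 trials per scenario, OR 2 / 2.5 / 3 / 4):
- Controls 85/10/4/1%: Fisher 16.9 / 28.0 / 33.6 / 44.6, rank 18.3 / 30.2 / 37.0 / 48.6. Loss 1.4 to 4.0 points.
- Controls 75/15/8/2%: Fisher 25.7 / 37.0 / 47.9 / 61.9, rank 30.3 / 43.8 / 54.0 / 69.4. Loss 4.6 to 7.5 points.

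**Fewer grades occupied.** With three grades (60/30/10/0%) the loss against chi-square is 6.2 to 8.3 points for OR 2 to 4. With two grades (60/40% or 70/30%) chi-square is level or up to about 3 points better. That is expected: in a 2 × 2 table the squared rank statistic is (N − 1)/N times the chi-square statistic, so the tests nearly coincide.

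**Effects that are not a one-direction shift.**
- Controls 50/25/15/10%, HCQ 70/5/15/10%: chi-square 74.8%, rank 31.8%. Here chi-square has more power.
- Controls 50/25/15/10%, HCQ 60/5/20/15%: chi-square rejects in 72% of trials, rank in 5%. P(HCQ lower) = 0.60 × 0.50 + 0.05 × 0.25 + 0.20 × 0.10 = 0.3325. P(HCQ higher) = 0.05 × 0.50 + 0.20 × 0.75 + 0.15 × 0.90 = 0.31. The net shift is about 2 points, yet chi-square is usually significant.

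**Fallback.** Wilcoxon on change in grade was compared with plain chi-square at OR 3, over four control distributions and assumed baseline–follow-up correlations of 0.3, 0.5 and 0.7. It had less power in 10 of the 12 scenarios. At correlation 0.5 it reached 20% vs 29% (85/10/4/1%) and 36% vs 48% (70/22/6/2%).

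**The case against.** The strongest reply is that the article fixes no test for diplopia. The chi-square/Fisher sentence is a general rule in a paragraph that opens with baseline characteristics, and the test for each secondary endpoint may be set in an analysis plan that is not shown. This stands in part. Diplopia is placed under the rule by inference, and a reader who concludes that the plan assigns it to chi-square by name goes beyond the text. Still, the stated rule is the only between-group rule that fits an outcome the article itself calls categories.

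Three other strong readings are not supported:
- *That diplopia will be analysed without baseline adjustment or an effect size.* The sentence on ANCOVA and regression promises both. It names no ordinal model, so it permits the right analysis without requiring it.
- *That the trial loses a fixed amount of power, or that the odds ratio of 4.3 implied by 12% and 37%, (0.37/0.63)/(0.12/0.88), applies to diplopia.* Those rates are planning values for the primary composite, whose improvement criteria are eyelid aperture, soft tissue and exophthalmos.
- *That the loss is worse because patients with mild disease cluster in low grades.* The calculations show the opposite: concentration at grade 0 generally shrinks it.

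**Conclusion.** The point holds as a minor improvement. The methods contain no rule for ordered outcomes, and by natural reading the Gorman score falls to an order-blind test. Under a one-direction shift, with controls between 85/10/4/1% and 40/35/15/10% and odds ratios of about 2 to 4, the cost is roughly 5 to 15 points of power against chi-square. It is about 1 to 4 points against Fisher in the sparsest case and nil with two occupied grades. Without a one-direction shift the ranking can reverse. None of these distributions or effects comes from the article. Diplopia is one of seven secondary endpoints and the trial was not sized on it.

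**What to change.** In Statistical methods, add that the Gorman grade at weeks 24 and 48 is compared between arms with a proportional-odds model containing treatment and baseline grade, reporting the common odds ratio with its 95% confidence interval. If the model cannot be fitted, use a Wilcoxon rank-sum test on the follow-up grade, stratified by baseline grade where possible (van Elteren). Do not use change in grade: it lost power in most scenarios checked, and it treats a step from 3 to 2 as equal to one from 1 to 0. Keep chi-square and Fisher for unordered variables.

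The cost is a sentence or two of text and no new data. The downside is the proportional-odds assumption.

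### The before-versus-after tests named for GO-QoL, CAS and unspecified variables cannot test HCQ against observation, yet stand unranked beside between-arm tests that can

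*Protocol article*

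**What the plan says.** The Trial design section of the protocol article sets a between-arm question. "This trial adopts a superiority framework", and the hypothesis is that adding HCQ "will result in superior ophthalmic outcomes compared to standard of care alone in patients with mild GO". On allocation: "The allocation ratio of randomization will be 2:1 in HCQ and control group, respectively".

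The Statistical methods section then lists several kinds of analysis:

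- **Between groups.** Student's t, chi-square or Fisher tests compare the treatment and observation groups. This sentence follows the description of baseline characteristics but is not restricted to baseline.
- **Before and after, GO-QoL and CAS.** The stated purpose is "To compare the scores of the GO-QoL and the CAS before and after treatment", by two-sided t-tests and Mann–Whitney tests. The t-tests are not called paired, and no arm is named.
- **Severity categories.** Proportions improved, stable and deteriorated are compared in both groups.
- **Before and after, unspecified variables.** "One-way repeated measures analysis of variance (ANOVA) will be used to analyze the change of variables before and after treatment".
- **Adjusted models.** In addition to the ANOVA, "ANCOVA and regression models will be used to adjust for baseline differences and estimate effect sizes with confidence intervals". No endpoint is assigned to them.

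A single two-tailed threshold of P < 0.05 closes the list.

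**The concern.** Two of the listed procedures do not fit the question as worded. A one-way repeated-measures ANOVA has time as its only factor. Without an arm term or an arm-by-time term it tests whether patients changed, not whether HCQ changed them more than observation did. Mann–Whitney assumes two independent samples, whereas scores before and after treatment come from the same patients.

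This matters more here than in a stable condition. The Background section says that about half of patients with mild GO improve naturally and about 20% may worsen, so change over time is not by itself a drug effect. The arms are also unequal: for the same natural change, a within-arm test has more power with 72 patients than with 36. If within-arm P values were interpreted, the larger HCQ arm would look better for a reason unrelated to the drug. Because valid and unsuitable tests share one threshold, the text gives no guard against that.

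**Working it through.** **1. The plan's own figure.** The Sample size section gives 12% and 37% improvement, 2:1 allocation, "a two-sided *α* of 0.05, and 80% power", and 72 + 36 patients. For two proportions with pooled variance and no continuity correction, with k = 2:

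n(control) = [1.96·√(p̄q̄(1 + 1/k)) + 0.8416·√(p₁q₁ + p₂q₂/k)]² / (p₂ − p₁)²

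- p̄ = (0.12 + 2 × 0.37)/3 = 0.2867, so p̄q̄ × 1.5 = 0.3067
- p₁q₁ + p₂q₂/2 = 0.1056 + 0.1166 = 0.2222
- n = (1.0855 + 0.3967)²/0.0625 = 35.2, rounded up to 36 control and 72 HCQ

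The figure reproduces (power 0.81). It concerns the primary composite only; no power is stated for the secondary endpoints.

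**2. Within-arm tests when the drug does nothing.** Inputs from the protocol: n = 72 and 36, two-sided 5%. Assumptions, since the protocol gives no SD or correlation: normal scores, SD 1, baseline-to-follow-up correlation 0.5, and the same spontaneous change in both arms. There were 4,000 simulated trials per row.

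| Common change (SD) | HCQ paired test significant | Control paired test significant | HCQ only | Control only | Both arms pooled, time only | Between-arm ANCOVA |
|---|---|---|---|---|---|---|
| 0.2 | 39% | 21% | 31% | 13% | 54% | 5.7% |
| 0.3 | 72% | 42% | 41% | 12% | 88% | 4.8% |
| 0.4 | 91% | 66% | 31% | 6% | 99% | 5.0% |
| 0.5 | 98% | 83% | 16% | 2% | 100% | 5.1% |

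The pooled column is the one-way repeated-measures ANOVA with two time points.

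Cross-check: at correlation 0.5 the SD of change is √(2(1 − 0.5)) = 1, so the paired t-test has noncentrality d√n. At d = 0.3 that is 2.55 for n = 72 and 1.80 for n = 36, giving power 0.709 and 0.417. The arms are independent, so P(HCQ only) = 0.709 × (1 − 0.417) = 0.413, in agreement with the simulation. At d = 0.2 and 0.4 the same calculation gives 0.304 and 0.325.

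With zero common change, the two one-sided patterns are equally frequent (4.7% and 4.8%). The tilt needs both spontaneous change and unequal arms.

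**3. Mann–Whitney on paired scores.** An unpaired test takes the variance of the mean difference as 2σ²/n; with correlation ρ it is 2σ²(1 − ρ)/n. The effective critical value is therefore about 1.96/√(1 − ρ). At ρ = 0.5 this is 2.77, a true type I error of about 0.6%. Simulation (3,000 runs per setting) gave 0.7% at n = 72 and 1.0% at n = 36; about 2% at ρ = 0.3; and below 0.1% at ρ = 0.7. For a 0.3 SD change at ρ = 0.5, power was 39% against 71% for a paired t-test at n = 72, and 16% against 41% at n = 36.

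**The case against.** The strongest reply is that the section already holds what is needed. A reader might infer that the plan cannot estimate an HCQ effect, or that the sound analysis is merely optional. The text supports neither: between-group tests are planned, and ANCOVA and regression are stated as things that will be done, with effect sizes and confidence intervals. Adding them to the ANOVA does not make them optional.

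A reader might also infer that every secondary endpoint is tested only before against after. The t-test and Mann–Whitney sentence names GO-QoL and CAS alone; the ANOVA sentence says only that variables are analysed. Nothing confines CT, diplopia, acuity, antibodies or serum markers to before/after testing.

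The Mann–Whitney sentence may be loosely worded. The secondary endpoint for GO-QoL is defined as a change, and an unpaired t-test with Mann–Whitney is a usual pair for comparing change scores between arms. That reading is plausible, but the sentence does not say it.

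Finally, nothing in the protocol says that significance on HCQ alone will count as benefit. The 31–41% applies only if someone reads the results that way. It also comes from correctly paired tests, so it should not be added to the Mann–Whitney problem, which loses power rather than creating false benefit.

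On ranking the analyses, an unseen SAP may do so, and its absence from an article would not alone be a fault. What remains is that the article names tests which, as worded, do not fit the data or the question.

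**Conclusion.** The point holds in a limited form. As written, the GO-QoL and CAS sentence applies an independent-samples rank test to paired scores, and the one-way repeated-measures ANOVA has no treatment term. Neither can address HCQ against observation, yet both stand at the same P < 0.05 threshold as between-arm analyses that can. The defect lies in the named before/after tests, not in the section as a whole.

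If within-arm results were interpreted, the tilt towards HCQ would be material: about 31–41% against 6–13% for the reverse over assumed common changes of 0.2 to 0.4 SD, falling to 16% against 2% at 0.5 SD. These figures rest on normal scores, a correlation of 0.5 and an identical change in both arms, none of which the protocol supplies. That between-arm ANCOVA holds about 5% does not depend on the size of the common change. This should be corrected, but it does not touch the primary composite or the sample size.

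**What to change.** In the Statistical methods section:

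1. State that the baseline-adjusted between-arm comparison at weeks 24 and 48 is the inferential analysis for GO-QoL, CAS and the other continuous secondary endpoints. This may be ANCOVA, as already planned, or a repeated-measures model with arm, visit and arm-by-visit terms and the baseline value as covariate.
2. Replace the one-way repeated-measures ANOVA with that model.
3. Report before/after change within each arm descriptively; if a test is shown, use a paired one.
4. If Mann–Whitney was meant to compare change scores between arms, say so; otherwise remove it from the before/after sentence.

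The cost is wording only. Baseline, week-24 and week-48 values are already scheduled, GO-QoL is also collected at week 12, and no extra patients are needed.
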